Our own phase II data suggested that postoperative chemoradiation may be beneficial for esophageal cancer patients (10). Thirty-eight lymph node positive (N1) patients underwent esophagectomy followed by postoperative chemotherapy (cisplatin, 5-FU, + epirubicin) and 50 Gy radiotherapy (CRT) and 28 (N1 patients) underwent surgery alone (S). Pre-operative risk factors, tumour characteristics, ECOG scores and lengths of stay were similar. Disease-free survival was similar (CRT 10.2 months vs. S 10.6 months) but the surgery alone group had more local recurrences (CRT 13% vs. S 35%). Overall Kaplan-Meier survival analysis showed a significant advantage with postoperative chemoradiation (log rank p=0.001). The median overall survival for the chemoradiation group was 47.5 months which was significantly longer than the surgery alone group (14.1 months). The three-year survival was 62% in the CRT group and 25% in the S group, and the five-year survival was 48% and 0% respectively.

Rice and colleagues from the Cleveland Clinic compared 31 patients with locoregionally advanced esophageal cancer (90% pT3, 81% pN1, and 13% pM1a) that received postoperative adjuvant chemoradiotherapy after resection to 52 patients that underwent esophagectomy alone (11). Patients received 50.4 to 59.4 Gy external beam radiation with concurrent two 4-day cycles of intravenous 5-fluorouracil (1,000 mg/m2/d) and cisplatin (20 mg/m2/d) during the first and fourth week of adjuvant therapy. Among propensity-matched patients, median, 1-year, and 4-year survivals for those receiving adjuvant therapy versus esophagectomy were 28 versus 15 months, 60% + 11% versus 65% + 11%, and 44%+11% versus 0% (P=0.05). Median time to recurrence was 25 versus 13 months (P =0.04), and recurrence-free survival was 22 versus 10 months (P=0.02). The authors concluded that patients with locoregionally advanced carcinoma after esophagectomy should be considered for adjuvant therapy.

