**11.0 Outcomes**

**11.1 Primary Outcome**

**Quality-of-Life** Quality-of-Life as measured by the FACT-E over 1 year from randomization.

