**12.1 Follow-up Schedule**

The follow-up visits will occur at the discretion of the treating surgical, medical, and radiation oncologists. All patients will be followed for events until 60 months or death. Routine care will include a history and physical and a chest radiograph. Quality-of-Life, toxicities and morbidity data will be completed only during the first year following randomization at baseline, and every 2 months up to 1 year.

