**15.0 Management of Intercurrent Events**

Several illnesses and major events may befall patients during the study. Referring physicians are free to treat each patient according to their best judgement. However, when in doubt they are encouraged to discuss an individual's management with the Thoracic Clinical Trials Centre.

The clinical course of esophageal cancer one in which a significant number of patients treated with standard therapy will deteriorate or die. Significant deterioration may be in the form of worsening symptoms of dysphagia, pain, anorexia, weight loss due to disease progression. The treating oncologist should always use the most appropriate management that is in the best interest of the patient.

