**17.0 Sample Size Determination**

**17.1 Sample Size**

The sample size is based on an improvement in the quality-of-life as measured by the FACT-E at one year. If we assume an improvement in the treatment arm of 15 points, 2- sided α=0.05, β= 0.2 and σ=25 (28)

Formula:

n per group = (Z_α_ + Z_β_)^2^ *2σ^2^

Δ^2^

σ=25

Δ=15

n=44 per arm.

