**17.2 Statistical Analysis**

Descriptive statistics were generated for all patients and stratified by treatment arm for baseline patient, tumour and treatment characteristics and stratified by treatment arm for HRQOL endpoints stratified by follow-up visit, compared using the chi-square test, Fisher’s exact test, two-sample t-test, Wilcoxon rank sum test or paired t-test (compared to baseline only) as appropriate. Univariable Cox proportional hazards regression was performed for OS and DFS for all eligible variables for all patients (Supplemental Table 1 online). Kaplan-Meier estimates were generated for OS and DFS for all patients and stratified by treatment arm compared using the stratified log-rank test stratified by clinical nodal status (N0, N1). All statistical analysis was intention-to-treat and performed using SAS version 9.4 software (SAS Institute, Cary, NC, USA) using two-sided statistical testing at the 0.05 significance level. The trial was not powered to detect differences in the secondary outcomes including survival. There was no imputing, deletion, guessing, or substitution used for missing values. There were no interim analyses. There was no blinding of patients, investigators, or data analysts to the treatment allocation.

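### Section 17.2 makes the primary FACT-E comparison one among survivors who return the form, calls it intention-to-treat, and does not say how death or a missing score enters it

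*Protocol*

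**What the plan says.** - **Endpoint.** Section 11.1 defines the primary outcome as "Quality-of-Life as measured by the FACT-E over 1 year from randomization". Section 12.1 collects it "at baseline, and every 2 months up to 1 year". Section 17.1 states: "The sample size is based on an improvement in the quality-of-life as measured by the FACT-E at one year".
- **Analysis.** Section 17.2 summarises the quality-of-life endpoints by arm and follow-up visit. It compares them with two-sample t, Wilcoxon or (against baseline) paired t-tests as appropriate. It adds "There was no imputing, deletion, guessing, or substitution used for missing values" and "All statistical analysis was intention-to-treat".
- **Death.** Section 7.0 follows each patient to death or one year and attributes outcome events to the assigned group. Section 15.0 expects that "a significant number of patients treated with standard therapy will deteriorate or die", and describes worsening dysphagia, pain, anorexia and weight loss.
- **Allowance for loss.** The sample-size summary in 17.1 adds 10% for loss to follow-up and does not mention death.

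No section gives a deceased patient a FACT-E value or rank, or names a longitudinal model, a composite or a sensitivity analysis for missing scores.

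**The concern.** A two-sample test at a given visit must leave out anyone without a score at that visit. The rule against deletion therefore cannot be met literally. What 17.2 produces is an observed-case comparison of patients who are alive and well enough to return the form. Each of them is analysed in the assigned arm, but the two groups compared are no longer the groups that were randomized.

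The losses are unlikely to be unrelated to the score. The symptoms that 15.0 lists as signs of deterioration overlap with what the FACT-E subscale measures (4.1: eating, appetite, swallowing, pain, weight loss). The timing of risk also differs by design. One arm has chemoradiation before surgery. The other has surgery first, with chemotherapy starting 8 to 12 weeks later and running for 12 weeks (sections 9.0 and 9.2.4).

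At stake is whether a FACT-E difference at one year can be read as a treatment effect rather than a difference in who was left to answer. In addition, a 12-month test makes no use of the earlier scores of patients who later die or drop out.

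**Working it through.** **1. The plan's own figure.** Inputs from 17.1: difference 15, "2- sided α=0.05, β= 0.2 and σ=25". The stated formula gives n = (1.96 + 0.842)² × 2 × 25² / 15² = 43.6, so 44 per arm, as stated. Adding 10% gives 44 × 1.1 = 48.4, stated as 48 (96 in total). The figure reproduces. It assumes that about 48 × 0.9 = 43.2 patients per arm have a one-year score (power 79.6%).

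**2. What the protocol says about early deaths.** It gives no rates by arm for the two strategies compared here. The Introduction offers two indirect sources:

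- A propensity-matched series of adjuvant therapy versus esophagectomy alone: "were 28 versus 15 months, 60% + 11% versus 65% + 11" percent at one year, so 40% and 35% dead.
- The investigators' own node-positive series: median survival 47.5 months with postoperative chemoradiation and 14.1 months with surgery alone. Assuming exponential survival, one-year mortality is 1 − 0.5^(12/47.5) = 16% and 1 − 0.5^(12/14.1) = 45%.

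Neither series has a preoperative arm, so neither gives the mortality gap for this trial.

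**3. Size of the bias when there is no true effect.** Assume a normal latent FACT-E with SD 25 and correlation ρ with survival. If a proportion p is lost, the mean of those remaining rises by

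ρ × 25 × φ(z_p) / (1 − p).

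At ρ = 1 (every loss is a lowest scorer) the rise is 6.86 for p = 15%, 10.59 for 25%, 12.42 for 30%, 14.25 for 35%, 16.10 for 40% and 17.99 for 45%. The spurious difference is ρ times the difference of two such values. For 15% versus 30% it is 0.3 × (12.42 − 6.86) = 1.67 and 0.7 × 5.56 = 3.89.

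The type I error of a nominal 5% test uses SE = 25 × √(1/n₁ + 1/n₂), with n = 48 × (1 − p), and equals Φ(−1.96 + d/SE) + Φ(−1.96 − d/SE). For 15% versus 30% at ρ = 0.7: SE = 25 × √(1/40.8 + 1/33.6) = 5.82 and d/SE = 0.67, giving 10.3%.

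| Loss, arm A v arm B (assumed) | Spurious gain for arm B, ρ = 0.3 | ρ = 0.7 | Type I error, ρ = 0.3 to 0.7 |
|---|---|---|---|
| 15% v 15% | 0 | 0 | 5.0% |
| 35% v 40% | 0.6 | 1.3 | 5.1% to 5.5% |
| 15% v 25% | 1.1 | 2.6 | 5.4% to 7.4% |
| 15% v 30% | 1.7 | 3.9 | 5.9% to 10.3% |
| 15% v 45% | 3.3 | 7.8 | 8.3% to 23.9% |

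If ρ = 0 the gain is zero in every row. At ρ = 1 the 35% versus 40% row gives 16.10 − 14.25 = 1.85.

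**4. Side effect on precision.** At 35% and 40% loss, 31.2 and 28.8 of 48 patients per arm would have a one-year score, and power for 15 points would be about 64%. This illustrates what a 10% allowance that omits death could miss. It is not a forecast for this trial.

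**The case against.** - **The direction is conditional.** Bias towards the arm with more deaths needs unequal losses and lower FACT-E in those lost. Section 15.0 supports the second condition; nothing in the protocol establishes the first. A reader might infer that the comparison is known to favour the arm with more deaths, or that the result could be reversed. The protocol supports neither, and no scenario above approaches 15 points. This stands.
- **The cited one-year survival is not this trial's.** A reader might carry 60% to 65% over. That series was 90% pT3 and 13% pM1a, whereas section 5.1 requires M0 and section 10.0 keeps pT1-2N0 patients in the analysis. Its 5-point gap implies only 0.6 to 1.9 points of bias. This stands.
- **Deaths are not ignored, nor are all earlier scores.** Section 17.2 compares overall survival by arm, and earlier scores enter the earlier visit comparisons. True, but neither brings a death into the FACT-E comparison, which is primary.
- **Intention-to-treat may mean only analysis as assigned.** Section 7.0 uses it in that sense, and observed scores are analysed by assigned arm. The wording can be defended; the analysis still omits randomized patients for reasons likely to be related to outcome.
- **The rule against imputation does not forbid a mixed model.** Correct: such a model imputes nothing. The problem comes from that rule together with the listed visit-wise tests.
- **This could sit in an analysis plan.** It could, had the protocol been silent. Instead 17.2 names the tests, rules out substitution and attaches the label.

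**Conclusion.** The point holds in conditional form. As written, 17.2 gives an observed-survivor comparison for the primary endpoint and no rule for death within the one-year window. The likely bias is about 1 to 4 points for loss gaps of 10 to 15 percentage points and ρ between 0.3 and 0.7, which is at most about a quarter of the 15-point target (3.9/15 = 26%). It reaches about 8 points only with a gap as wide as 15% versus 45%, and vanishes if losses are equal or unrelated to FACT-E. Type I error exceeds 10% only with a wide gap or strong correlation.

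All loss rates and correlations are assumptions, and the normal model with SD 25 retained among survivors is an approximation. Sick survivors who do not return forms act in the same way as deaths; the protocol gives no rate for them.

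**What to change.** In 17.2:

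1. Make the primary FACT-E analysis a likelihood-based repeated-measures mixed model using all observed scores of all randomized patients, with the arm contrast at 12 months, the time point on which 17.1 bases the sample size.
2. Add a supporting 12-month rank comparison in which death ranks below every observed score. This is needed because the mixed model implicitly extrapolates scores past death and so does not by itself settle how death counts.
3. Report the numbers alive and the numbers completing FACT-E by arm and visit.
4. Keep the visit-wise tests as descriptive, and label them observed-case rather than intention-to-treat. Reword the missing-values sentence to match, since a test on observed scores cannot avoid omitting missing ones.

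The cost is wording and modest programming. Scores are already collected every two months (12.1) and every death is documented (12.2). There are two downsides. The rank composite mixes survival with quality of life, so it should stay supportive. And 17.2 is written in the past tense: if the analysis has already been done, the added analyses must be labelled post hoc.

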**17.3 Data Monitoring**

In case the trial has a dramatic effect early in the study, the investigator team has agreed to provide an interim analysis when the first 50 patients have passed the one year follow up, and if there is either a benefit, or a serious worsening of one group relative to the other. The data management centre will do the interim analysis and share it with the Safety Monitoring Committee to decide whether to stop the trial earlier than planned. While many may suggest that some adjustment for an interim analysis is needed; Pocock (51) and an article (52) have suggested that this is not necessary when the number of interim analyses is few (less than 2); and the level of interim analysis is at most 1%. Hence we propose the Type 1 error criterion for stopping early will be 1%, with no adjustment of the final alpha level if the trial is not stopped early (28,29).

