**16.0 Participant Safety and Confidentiality**

The study physicians will be responsible for the safety or participants under his or her care. The Steering Committee will have primary responsibility for the monitoring of study data for adverse trends and morbidity. The confidentiality of all participants will be protected both at the study site and the Study Coordinating and Methods Center. Completed data collection forms will receive the same protection as other medical records. Reporting of study results will not identify individual patients.

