**20.0 Feasibility of Recruitment**

Pilot work from London has demonstrated that the procedure can be done safely with encouraging results (10). Approximately 50 esophagectomies occur in London each year. If London is the only centre, it will take two years to accrue the required number of patients.

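### Sections 17.2 and 17.3 contradict each other on whether there is an interim analysis; if the look in 17.3 is taken, the overall two-sided type I error is about 0.054, not 0.05

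*Protocol*

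**What the plan says.** Section 17.2 (Statistical Analysis) states "There were no interim analyses" and describes the analysis as performed "using two-sided statistical testing at the 0.05 significance level". It is written throughout in the past tense.

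Section 17.3 (Data Monitoring) looks forward. It states that "the investigator team has agreed to provide an interim analysis when the first 50 patients have passed the one year follow up", adds a clause about a benefit or a serious worsening of one group relative to the other, and sends the result to a Safety Monitoring Committee "to decide whether to stop the trial earlier than planned". On error control its rule is "the Type 1 error criterion for stopping early will be 1%, with no adjustment of the final alpha level if the trial is not stopped" at that look. It argues from cited sources that adjustment is unnecessary when interim analyses are few and the interim level is at most 1%.

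Section 17.1 sets the total at 96 patients (48 per arm after adding 10% to 44). Section 20.0 says that, with London as the only centre, "it will take two years to accrue the required number of patients", and puts the local volume at about 50 esophagectomies a year.

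**The concern.** Two adjacent sections give opposite answers on whether the primary endpoint, FACT-E at one year, is tested once or twice. A separate analysis plan could not settle this, because the protocol itself takes both positions.

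The answer determines the error rate. A single test at 0.05 has level 0.05. A look that can stop the trial at 0.01, followed by a final test still at 0.05, has two chances to reject, so its overall level must exceed 0.05. Section 17.3 says that no adjustment is needed, which can be checked by direct calculation.

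Two features of 17.3 add to the problem. The clause on benefit or worsening leaves unclear whether the look is always done or done only when a difference is already apparent. And the timing, set against section 20.0, bears on what the look could achieve.

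**Working it through.** **Inputs**
- Final test: two-sided 0.05 (17.2).
- Interim: after 50 patients have one year of follow-up, stopping at 1% (17.3). Sidedness is not stated; it is taken as two-sided because 17.3 covers both benefit and worsening.
- Δ = 15, σ = 25, power 80%, 44 per arm, 48 per arm and 96 in total after adding 10% (17.1).
- Accrual: the required number in two years, so 96/2 = 48 a year; about 50 esophagectomies a year (20.0).

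**The protocol's own figure.** n per arm = 2σ²(z₀.₉₇₅ + z₀.₈₀)²/Δ² = 2 × 625 × (1.960 + 0.842)²/225 = 43.6, rounded up to 44. Then 44 × 1.10 = 48.4, stated as 48, and 2 × 48 = 96. The stated size is reproduced.

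**Overall type I error if the look is taken.** Under the null, the interim and final statistics Z₁ and Z₂ are approximately bivariate normal with correlation √t, where t is the information fraction. With t = 50/96 = 0.521, √t = 0.722, and

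P(|Z₁| > 2.576 or |Z₂| > 1.960) = 0.0543.

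A simulation of 4 million trials gave 0.0545. The result is not sensitive to t:

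| Information fraction | Overall two-sided error |
|---|---|
| 45/96 = 0.469 | 0.0549 |
| 50/96 = 0.521 | 0.0543 |
| 50/88 = 0.568 | 0.0538 |
| 50/86 = 0.581 | 0.0536 |

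**If the look is not taken.** There is one test at 0.05, so the level is 0.05.

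**Settings that hold 0.05 with a look**
- Interim level 0.01: solving for the final level at t = 50/96 gives 0.0455 (critical |Z| about 2.00); the range is 0.0448 to 0.0460 for t from 45/96 to 50/88. With 44 per arm the expected Z is 15/(25 × √(2/44)) = 2.814. Power of the final test is therefore Φ(2.814 − 1.960) = 80.4% at 0.05 and Φ(2.814 − 2.000) = 79.2% at 0.0455.
- Interim level 0.001 with final level 0.05: overall error 0.0502 at t = 50/96.

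**Timing.** With uniform accrual of r a year, enrolment closes at 12 × 96/r months and the look is due at 12 × 50/r + 12 months. The number enrolled when the look is due is the smaller of 96 and 50 + r. The two dates coincide when 50 + r = 96, that is, r = 46.

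| Accrual per year | Enrolment closes (month) | Look due (month) | Still to enrol |
|---|---|---|---|
| 50 | 23.0 | 24.0 | 0 |
| 48 | 24.0 | 24.5 | 0 |
| 46 | 25.0 | 25.0 | 0 |
| 40 | 28.8 | 27.0 | 6 |
| 30 | 38.4 | 32.0 | 16 |
| 24 | 48.0 | 37.0 | 22 |

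**The case against.** The strongest defence is that 17.2 reads as a record of completed work and 17.3 as the plan that preceded it. On that reading no look was taken, one test was done at 0.05, and only the text was left unharmonised. This largely stands. A reader might infer that the trial's 0.05 level was not delivered; the documents do not support that, because the inflation arises only if the look was taken and 17.2 says that it was not. What does not stand is leaving both sentences in force, since nothing in the protocol says that the plan in 17.3 was dropped.

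A second defence is that the inflation is only about 0.4 percentage points and that the choice is disclosed and argued for. Its small size is a fair reason against a higher severity. It does not rescue the claim that no adjustment is needed while the stated level is 0.05.

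Some stronger readings should also be resisted:
- A reader might infer that the look could never stop recruitment. That rests on a margin of 0.5 to 1 month and reverses below 46 patients a year; 48 a year would mean randomizing about 96% (48/50) of the local esophagectomies. Section 17.3 also speaks of stopping the trial, not recruitment alone, so a late look could still affect ongoing treatment or reporting.
- The clause on benefit or worsening might be taken to mean that by-arm data must be inspected to decide whether to look. It can equally describe what would justify stopping. It is ambiguous, and no more than that.
- Section 16.0 says "The Steering Committee will have primary responsibility for the monitoring of study data for adverse trends and morbidity", while 17.3 names a Safety Monitoring Committee. General monitoring and a decision on one interim result are different functions and can coexist.
- Low power at the look for a 15-point difference is not a defect, because the look is meant for a dramatic effect.

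**Conclusion.** The contradiction between 17.2 and 17.3 is established on the text. Its statistical consequence is conditional: about 0.054 overall if the look is taken under the 17.3 rule, and 0.05 if it is not. The 0.054 assumes a two-sided 1% criterion, approximately normal statistics and an information fraction near one half; the range 0.0536 to 0.0549 covers reasonable alternatives.

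The timing point is secondary. At 96 patients in two years with uniform entry, the look comes about half a month after enrolment closes and would save no enrolments. It would save few at moderately slower rates: 6 at 40 a year and 22 at 24 a year.

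Severity: should-fix. The protocol must state clearly how many times the primary hypothesis is tested and at what level, but the documents show no actual loss of error control.

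**What to change.** Keep one statement.

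- **No look.** Delete the efficacy interim from 17.3, state that none was done, and retain safety review. The final test stays at 0.05. At the planned accrual this gives up no ability to stop enrolment; at slower accrual it gives up a little.
- **Look retained.** Delete the sentence in 17.2. Reword the benefit-or-worsening clause so that the analysis is done unconditionally at 50 patients with one year of follow-up. State that the interim criterion is two-sided. Replace "with no adjustment of the final alpha level if the trial is not stopped early" with one of two pairs: 0.01 at the look and about 0.0455 at the end, recomputed for the information fraction actually reached; or 0.001 at the look and 0.05 at the end (overall 0.0502).

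Either way the change is about one paragraph. The 0.01/0.0455 pair costs about one percentage point of final-test power (80.4% to 79.2% at 44 per arm). The 0.001 pair leaves the final test unchanged but makes early stopping harder. Removing the look costs nothing in power.

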**18.0 Trial Organization**

The proposed trial will be conducted in London, Ontario. Ottawa and Vancouver have expressed interest and may join. Policy decisions relating to the trial will be decided by the Steering Committee. The day-to-day coordination and central randomization will be provided by the Thoracic Clinical Trials Office at the London Health Sciences Centre, Victoria Hospital, London, Ontario.

